The spread of mobile telephones throughout sub-Saharan Africa affords an important opportunity to address these inefficiencies and retain quality care. Text messages show immense promise to positively influence health behavior and improve clinical care [30-32]. Most short message service (SMS)-based health promotion efforts use one-way ‘push’ messages, blasting pre-defined messages to many people simultaneously [33-35]. Among VMMC programs, a randomized control trial determined that automated SMS modestly increased adherence to 7-day follow-up visits from 59.7% to 65.4% (RR 1.09, 95% CI 1.00–1.20; p = 0.04) but did not influence resumption of sex during the 42-day healing period (relative risk=1.13, 95% CI 0.91-1.38, p=0.3) [29, 36]. An important weakness of these one-way, blast approaches is the one-size-fits-all approach, removing patients’ ability to communicate back with healthcare workers [37], potentially reducing patient engagement in care.

Two-way texting (2wT) between providers and patients shows promise to provide quality interactive care. In Kenya, patients enrolled in a SMS study significantly increased adherence and viral load suppression, but high-volume, manual texting was time-consuming and not sustainable for healthcare workers [38]. Another Kenyan study engaged patients in important health-related conversations and provided critical health information [39]; however, this intervention tasked the health workers to respond to complicated, open-ended questions, investing considerable time. In 2008 members of this study team pioneered an alternative approach to provide high-quality, efficient, coordinated service by enabling patients or community health workers to exchange ad hoc messages with facility-based nurses in Malawi [40, 41]. **Use of interactive, mobile technology that improves both care quality and care efficiency for providers and patients is warranted.**

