# 3. GOAL AND OBJECTIVES

**We propose to maintain patient safety while reducing the substantial VMMC follow-up workload burden** by using two-way mobile phone texts to provide in-person review only for men who indicate a desire or need for follow-up. This tailored approach to post-procedure VMMC care could reduce unnecessary visits and remove barriers for VMMC clients without deterioration of quality care. ZAZIC’s diverse, expert team of researchers from the University of Washington, Seattle, USA; the University of Zimbabwe; Medic Mobile, Nairobi, Kenya; and Zimbabwean partner organizations will test this mHealth intervention. We believe that bi-directional, interactive, text-based short message service (SMS) during the most critical 14 days after circumcision will help men identify and act on any sign of an adverse event, thereby seeking in-person follow-up only when an AE is suspected and reducing unnecessary visits. **Reduced in-person follow-up could also free healthcare workers to perform additional VMMC surgeries.** Using a prospective, randomized control trial (RCT), our intervention compares two groups of clients with cell phones: 1) standard care (control group) and 2) clients who receive and respond to a daily text with in-person follow-up only if desired or if an AE is suspected (intervention). Both arms complete a study-specific, Day 14, in-person, follow-up review for verification of self-reports (intervention) and comparison (control). Our specific objectives are to:

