Study preparation: We will conduct a rapid situation analysis with healthcare workers, VMMC clients, and stakeholders to assess suitable responses to VMMC client texts, setting standards for text responses and in-person follow-up. We will modify existing usability surveys for this public health context. A small pilot with 50 VMMC clients who will be enrolled in the texting intervention will include usability testing with both 2wT clients and nurses implementing the 2wT system, illuminating system experiences from both perspectives. Usability results will inform in-box modification, message format preferences (SMS or WhatsApp) and optimal message delivery (timing, frequency, language preferences). Experience from study coordinator and other team members will add detail to inform 2wT adaptation and modification of Standard Operating Procedures before implementation. We will examine local infrastructure (e.g. electricity and cell network), and explore 2wT cost reduction options (e.g., text bundling, free-call back numbers) and adapt accordingly

**Standard** VMMC care (Control arm): For the 361 men randomized into the control arm, ZAZIC follows all MoHCC protocols based on WHO guidelines [8] including routine surgical VMMC follow-up on post-surgery days 2, 7 and 42 (Table 1). Patients may seek care outside scheduled visits for suspicion of AEs at any healthcare facility at any time but most often return to their VMMC site. Referral cards for VMMC clients provide local numbers for patients to text, call, or request a call back for emergencies. A standardized approach is used to assess, identify, and record the severity of AEs [45]. All VMMC care, from assessment of all AEs through complete healing, is provided free to clients from MoHCC. Clients who do not return to the clinic for follow-up on Day 2 or Day 7 are traced: 3 attempts by phone and then up to 3 attempts at in-person tracking after which they are considered lost to follow-up (LTFU) [46]. There is no tracing for Day 42 visits. For the purposes of this study, control arm VMMC clients will be asked to come in on Day 14 for an additional follow-up visit. No active follow-up is provided at Day 14.

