VMMC care procedures (2wT arm): We will conduct a prospective, un-blinded, randomized control trial (RCT) among VMMC clients in a 1:1 ratio of control to intervention. Study participants and clinic staff are not masked to treatment. For the 361 men randomized into the intervention arm, men in the 2wT will receive routine VMMC surgical care and counseling, including referral cards for emergencies. 2wT clients will receive automated daily texts from days 1-14 (Table 1 and Figure 3). It is free to receive call and texts; it costs $0.05 to send a SMS in Zimbabwe [58]. If they respond that they suspect no adverse event, no immediate follow-up action will be taken. If a 2wT VMMC client responds affirmatively to any daily text that he suspects an AE, a VMMC nurse will exchange modifiable, scripted texts with the client to determine the symptoms, frequency, and severity. Then, if deemed necessary, the client will be asked to return to clinic the following day or earlier if an emergency is suspected. AE management will adhere to MoHCC standard care. If 2wT patients do not respond to texts on Day 2 or Day 7, the same MoHCC tracing process will be activated, after which they will be considered LTFU. All study participants will be asked to come to the clinic for study-specific, Day 14 follow-up to review healing and verify adverse event reporting. Day 14 was chosen for verification because 95% of all AEs within the ZAZIC VMMC program are reported Day 14 or earlier [44], suggesting that most AEs have occurred by this time point. In a previous field study of AEs, the most common AEs of bleeding and infection were found a mean of 6.7 and 9.0 days, respectively, after VMMC [20], further supporting the 14 day period used in this and a previous study[13]. The Day 14 review will be conducted by routine VMMC providers according to MoHCC review guidelines. At Day 42, we will implement a brief text-based survey with 2wT clients to ascertain complete healing, providing stronger inferences at study completion.

[figure not shown]

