**For Objective 1**, the 2wT safety outcome of interest is cumulative AE rate (moderate or severe) ≤ Day 14. Incidence of AEs before Day 14 will be extracted from routine VMMC data for both 2wT and control. Incident AEs on Day 14 will be identified, classified, and graded for severity using routine MoHCC protocols [9] and recorded on routine VMMC AE forms. We will compare cumulative rates of any moderate or severe AE ≤ Day 14 between groups using Fisher’s exact test as the expected number of AEs is low. The rates will be calculated per arm as: (# moderate + severe AEs)/ (total # VMMC clients who attend/responded to 2, 7 or 14 Day follow-up visits or texts). Multivariate logistic regression models (any AE v none) will quantify the magnitude of difference, adjusting for any potential confounders. To determine follow-up visit reduction, we will compare the mean number of in-person visits for intervention and control using a t-test. A multivariate linear regression model will further quantify the effect of intervention on visit reduction, adjusting for potential confounders. Secondary outcomes include: AE rates on Day 14, texting response rate, time between 2wT AE text reporting and follow-up, severity of AEs. We will perform appropriate summaries of missing data and LTFU, testing for systematic differences in response by study arm. *We hypothesize that 1) 2wT is non-inferior to routine follow-up for patient safety and that 2) 2wT* *will reduce unnecessary follow-up over standard care.*

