Capacity Building and Sustainability**:** ZAZIC is, with the exception of one in-county I-TECH employee, entirely run through true local organizations, demonstrating considerable experience in collaboration and capacity building. ZAZIC’s MoHCC partnership also enhances local ownership and buy-in, helping ensure replication of the mHealth intervention if successful. Frequent communication and team-based decision making among all members of the multinational, multidisciplinary team will help strengthen mHealth research capacity at I-TECH/Zimbabwe, University of Zimbabwe, and local NGO partner, ZiCHIRe. By working closely with researchers from the UW and Medic Mobile, Drs. [name] and [name] will gain mHealth research and implementation capacity, helping translate findings to public health policy. Through their leadership in this research, they will become mHealth leaders in Zimbabwe, creating a local team of researchers for scale-up and evaluation. Partnering with Medic Mobile in Nairobi, integrating with their existing software platform and building an expanded, local open source community will afford distinctive advantages for long-term maintenance and expansion. [name] has already significantly contributed to research design and will continue to gain research skills from attendance at the mHealth conference in Year 2 to present results of and build research collaborations.

Future plans**:** If texting with VMMC clients is found to be non-inferior to routine, in-person follow-up for detection of AEs, scale up could dramatically reduce time spent on unnecessary VMMC follow-up visits by healthcare personnel and decrease the burden on VMMC clients. Future funding could enable scale-up of the intervention in other high volume VMMC sites with high mobile phone coverage, conducting additional rigorous evaluation in diverse field and clinical contexts. We would seek funding to test 2wT among rural populations or smaller urban areas. Lastly, we will explore how 2wT could be integrated into DHIS2, the national health information system, to improve and ease reporting.

Innovations

- Replace in-person follow-up visits with 2wT interaction between patients and providers holds potential to dramatically reduce the burden on the health system at low cost while maintaining patient safety. This rigorous research involving local researchers is needed to test and optimize the approach.

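### The Day 14 visit is the only scheduled examination both arms share by the primary endpoint, but men who miss it are not traced, so AE ascertainment may differ by arm

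*Protocol*

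**What the plan says.** All places are in the Protocol.

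- **Role of Day 14** (Goal and Objectives): "Both arms complete a study-specific, Day 14, in-person, follow-up review for verification of self-reports (intervention) and comparison (control"). Study Procedures repeats that the visit serves to review healing and check AE reporting.
- **Control arm** (Study Procedures, standard care): routine visits on Days 2, 7 and 42. "Clients who do not return to the clinic for follow-up on Day 2 or Day 7 are traced", with up to three phone and then up to three in-person attempts. Day 42 is not traced. Control men are asked to attend Day 14, and the paragraph ends "No active follow-up is provided at Day 14".
- **2wT arm** (Study Procedures, 2wT care): daily automated texts on Days 1 to 14. "If they respond that they suspect no adverse event, no immediate follow-up action will be taken". Tracing is tied to texts: "If 2wT patients do not respond to texts on Day 2 or Day 7, the same MoHCC tracing process will be activated". Nothing is said about tracing a missed Day 14 visit.
- **Outcome data** (Data Analysis, Objective 1): "Incidence of AEs before Day 14 will be extracted from routine VMMC data for both 2wT and control". The denominator of the AE rate is every client with at least one attended visit or answered text at Day 2, 7 or 14.
- **Decision rule** (Sample size): margin 1.6 percentage points. 2wT is declared non-inferior if an AE rate above 2% can be ruled out.
- **Use of the result** (Future plans): scale-up is discussed for the case that texting is "found to be non-inferior to routine, in-person follow-up for detection of AEs".

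**The concern.** The two arms find AEs before Day 14 by different routes. A control man normally enters the analysis because a clinician has looked at him. A 2wT man can enter because he sent a text. The Day 14 examination is the design's answer to that difference, and it works only if nearly everyone attends, or if non-attenders are pursued equally in both arms. The protocol provides for no such pursuit.

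This matters more here than in a superiority trial, because fewer recorded 2wT events help the trial succeed. An AE that was neither reported nor seen counts as a success for the intervention. A later analysis can describe the gap but cannot recover events that nobody looked for.

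For the same reason, the phrase in Future plans does not fit the test. A low recorded rate is compatible with good safety or with poor detection, so it cannot show that detection is non-inferior.

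**Working it through.** **1. Reproduce the plan's figure.** Implied control rate: 2.0% − 1.6% = 0.4%. With one-sided alpha 2.5% and 90% power:

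n = (1.960 + 1.282)² × 2 × 0.004 × 0.996 / 0.016² ≈ 327.04, rounded up to 328 per arm.

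328 × 1.10 = 360.8, or 361, as stated. (Dividing by 0.90 would give 365; the difference is immaterial here.) The sample size is not the problem. After 10% loss, 361 × 0.90 ≈ 325 men per arm are evaluable.

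**2. Who is examined by Day 14.**

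| | Control | 2wT |
|---|---|---|
| Scheduled examination, Days 2 and 7 | yes | only if wanted or an AE is suspected |
| Trigger for tracing | missed Day 2 or 7 visit | unanswered Day 2 or 7 text |
| Day 14 examination | asked to attend | asked to attend |
| Tracing if Day 14 is missed | stated as none | none described |
| Minimum needed to enter the denominator | one visit at Day 2, 7 or 14 | one visit, or one text, at Day 2, 7 or 14 |

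Day 14 is therefore the only scheduled examination the arms share by the endpoint.

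**3. What is known about attendance.** Background gives over 95% attendance at Days 2 and 7, which are traced, and just over 30% at Day 42, which is not. Day 14 is untraced, but willingness to attend is an inclusion criterion and attendance earns a $5 airtime credit in both arms. The protocol gives no figure for Day 14, and none can be derived.

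**4. Size of the effect if 2wT events are lost.** Set the control recorded rate at 0.4% and the true 2wT rate at 2%, exactly at the margin. Recorded 2wT rate = 2% × share recorded. I enumerated all outcomes for 325 per arm and applied a score test with the variance constrained at the margin of 1.6 points, one-sided 2.5%. The choice of score test and the recorded shares are my assumptions. The last column is the normal approximation, Φ[(0.016 − (p − 0.004))/SE − 1.960], where p is the recorded 2wT rate and SE² = (0.004 × 0.996 + p(1 − p))/325.

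| Share of 2wT AEs recorded | Recorded 2wT rate | Expected recorded AEs in 325 | False non-inferiority, score test | Normal approximation |
|---|---|---|---|---|
| 100% | 2.0% | 6.5 | 1.6% | 2.5% |
| 90% | 1.8% | 5.85 | 2.6% | 4.3% |
| 80% | 1.6% | 5.2 | 4.2% | 7.4% |
| 50% | 1.0% | 3.25 | 17% | 33% |

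The expected count at the margin is about 6.5 events, so losing one to three of them moves the error rate visibly.

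**The case against.** **Direction.** The strongest objection is that the bias need not favour 2wT. Background describes the texting system as active surveillance. The daily prompts run to Day 14 and may raise both AE reporting and Day 14 attendance in 2wT. Control men have no scheduled contact between Day 7 and an untraced Day 14, while a cited field study puts infection at a mean of 9.0 days. Control AEs from Days 8 to 14 could be the ones lost, which would work against 2wT. This stands: the direction cannot be known in advance. It does not remove the point, because ascertainment that may differ either way still distorts the comparison.

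**Size.** A reader might take the Background trial of one-way messages, which "increased adherence to 7-day follow-up visits from 59.7% to 65.4"%, as the likely Day 14 attendance and conclude that over a third of each arm goes unexamined. The documents do not support that: it is another programme's Day 7 visit, and this trial adds a willingness criterion and airtime. A reader might also infer that a clearly unsafe 2wT arm would usually pass. That needs AE rates well above the protocol's planning values and a recorded share near a quarter, which missing Day 14 tracing alone would not produce. If s is the share found by text or self-presentation, a the Day 14 attendance and p the share still recognisable at Day 14, the recorded share is s + (1 − s)·a·p. Even at a = 0.60, s = p = 0.5 gives 0.5 + 0.5 × 0.60 × 0.5 = 0.65, and s = 0.8 with p = 0.5 gives 0.8 + 0.2 × 0.60 × 0.5 = 0.86. The upper rows of the table are the more plausible ones.

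**Detection claim.** The stated hypothesis concerns the AE rate and patient safety throughout Objective 1. The detection wording appears once, in Future plans. It is a phrase to correct, not a planned inference.

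**Already handled.** The Day 14 AE rate is a secondary outcome, and loss to follow-up will be compared by arm. The appendix list names visit procedures, call and text scripts and a Day 14 register that are not shown. The comparisons can reveal a difference but cannot correct it. The unseen appendices may contain part of the remedy, but the main text as it stands rules out active follow-up for control men.

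**Conclusion.** The point holds as a low-cost improvement. The visit meant to verify self-reports is not secured in either arm, and the denominator counts unexamined 2wT texters as AE-free. Ascertainment may differ by arm in an unknown direction; loss in 2wT is the direction that would produce a false non-inferiority finding. At the protocol's implied rates the effect is modest if 80 to 90% of 2wT AEs are recorded (2.6 to 4.2%, against 1.6% with full recording) and material at 50% (17%).

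This rests on a control rate of 0.4% with complete control recording, a true 2wT rate of 2%, 325 evaluable men per arm, the score test, and assumed recorded shares. It also reads silence about Day 14 tracing in the 2wT paragraph as absence of tracing. The documents do not support a claim that the result will be biased towards 2wT, or that attendance will be poor.

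**What to change.** 1. In Study Procedures, replace the sentence denying active follow-up at Day 14. Apply the existing three phone attempts to Day 14 non-attenders in both arms, inviting each man to the Day 14 examination. If he still does not attend, complete one scripted AE checklist covering Days 1 to 14 and care sought at any facility, identical in both arms.
2. Report Day 14 examination completion by arm, and AEs first found at Day 14 that had not been reported by text.
3. Add a sensitivity analysis of the primary comparison restricted to men with verified Day 14 status. It selects men after randomisation, so it supports the primary analysis and does not replace it.
4. In Future plans, refer to the recorded AE rate in place of detection of AEs.

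Cost: a short amendment and extra phone calls for the existing coordinator, using contact details already collected at enrolment. The number of calls depends on Day 14 attendance, which is unknown. A phone report is weaker than an examination, so the checklist narrows the gap without closing it.

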Building upon these previous mHealth initiatives, we seek to implement a two-way texting (**2wT**) intervention that **combines automated and interactive text messaging to maintain safety while dramatically reducing the burden that in-person VMMC follow-up places on weak health systems.** Automated messaging during Days 1-14 after circumcision could track men who are healing without complication, enabling a conservative estimate of more than 80% of clients to avoid unnecessary in-person follow-up at post-operative Days 2, 7 and 42. When a patient responds to an automated prompt message in a way that flags a potential AE, interactive messaging with a nurse would encourage them to promptly seek in-person, follow-up care. 2wT would act as active but efficient surveillance, improving care. By combining automated messaging to screen out cases with no complications and interactive texting to identify potential AEs, this intervention could make the care pathway far more efficient, reducing the costs of VMMC care over time for both providers and patients. **Reduced in-person follow-up could also free these same healthcare workers to perform additional VMMC surgeries.**

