**Objective 1: Determine if 2-way texting can safely reduce VMMC follow-up visits**

Approach: Un-blinded, prospective, non-inferiority, RCT in high-volume facilities providing VMMC. Two-way texting (**2wT**) will provide interactive, text-based follow-up. 2wT men healing without complication could decline in-person follow-up; those with suspected AEs will be referred to in-person care. We will compare the safety outcome of combined moderate or severe AE rate ≤ Day 14 post-VMMC and the workload outcome of average number of in-person follow-up visits between control and intervention arms.

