Risks for HCW: This study carries minimal risk for HCW. Risks in this study are low relative to the potential for improvement in health and quality of healthcare services that could arise from the research. HCW will be informed that there are limited risk associated with the intervention and data collection procedures. Some HCW participating in interviews may feel uncomfortable answering questions about quality of health care services, HCW responsibilities, intervention quality, or other areas of inquiry.

Injury/side effects/adverse events: All routine VMMC surgical procedures will be followed for this study. Any additional MC-related risk that may be incurred by participants by virtue of their text-based follow-up will be monitored closely and managed as described above. Adverse event (AE) management will be conducted according to MoHCC guidelines, including assessment of the severity, type, and treatment plan. Participants will be allowed to seek in-person follow-up at any time, as with the control arm, as per MoHCC guidelines. Participants will also be informed that they can withdraw from the study at any time with no repercussions.

Discomfort/stress: Individuals who consent to participate may experience mild discomfort or stress as they will be asked to discuss topics that may be sensitive, including their VMMC method choice and rationale. We will prevent undue influence by stressing the voluntary nature of this study and each person’s ability to decline without any risk to their VMMC service quality.

Procedures for minimizing risk to participants include:

1. For AE management, AEs will be managed according to MoHCC guidelines. The 2wT study nurse will urge in-person follow-up for any 2wT intervention arm participant who is concerned about any possible AE. The participant will be instructed to return to the study site or the nearest hospital in case of any unexpected event, for example if there is severe discoloration of the penis, signs of infection (purulence), severe or increasing pain, wound opening, or any other significant concern that they may have. In the event of a complication meeting the case definition for a clinical AE associated with the VMMC, the provider will document the complication in the VMMC register and client intake form according to the guidelines. Mild post-operative infections will be managed with wound cleansing and dressing, and antibiotics will be prescribed where clinically indicated.

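### The protocol gives two incompatible rules for a texting-arm man who reports a suspected AE: return only if the nurse judges it necessary, or in-person review urged for any concern

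*Protocol*

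**What the plan says.** Five places in the protocol describe what happens when a 2wT man reports a possible AE.

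- **Section 4, Study Procedures (care in the 2wT arm).** After an affirmative text, "a VMMC nurse will exchange modifiable, scripted texts with the client to determine the symptoms, frequency, and severity". The next sentence reads: "Then, if deemed necessary, the client will be asked to return to clinic the following day or earlier if an emergency is suspected".
- **Section 5, procedures for minimizing risk, item 1.** "The 2wT study nurse will urge in-person follow-up for any 2wT intervention arm participant who is concerned about any possible AE". The same sentence appears again under Protection against Risk.
- **Section 3, Objective 1.** "those with suspected AEs will be referred to in-person care".
- **Section 2, background.** When a reply flags a potential AE, "interactive messaging with a nurse would encourage them to promptly seek in-person, follow-up care".

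The Objective 1 outcomes are defined under Data collection / Data analysis in Section 4. The safety outcome is the cumulative rate of moderate or severe AEs to Day 14; the workload outcome is the mean number of in-person visits. On the source of AEs: "Incidence of AEs before Day 14 will be extracted from routine VMMC data for both 2wT and control". On who records them, Section 5 says "the provider will document the complication in the VMMC register and client intake form according to the guidelines". The denominator of the AE rate is the "total # VMMC clients who attend/responded to 2, 7 or 14 Day follow-up visits or texts".

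**The concern.** The trigger is the same in all five places, but the required action differs. In Section 4 the return visit depends on the nurse's judgement after a text exchange. In Section 5 it is urged for anyone with a concern. A man with the same message could be settled by text under one rule and urged to attend under the other.

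Three things depend on the rule. It is the core of the intervention, so a non-inferiority result would not describe one defined procedure. It is the participant safeguard offered in the ethics section, and the operative procedure does not match that safeguard. It also feeds the outcomes: the visit count directly, and the AE count potentially, because an AE reaches the numerator only through a provider's record.

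**Working it through.** **1. The rules side by side**

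| Place in protocol | Trigger | Action |
|---|---|---|
| Section 4, Study Procedures | Affirmative daily text | Text assessment; return only if the nurse judges it necessary |
| Section 5, risk item 1 | Concern about any possible AE | In-person review urged, no condition |
| Section 5, Protection against Risk | Same | Same |
| Section 3, Objective 1 | Suspected AE | Referred to in-person care |
| Section 2 | Reply flags a potential AE | Encouraged to seek in-person care promptly |

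The first row stands alone, and it is the row that describes the procedure. The documents do not settle which rule is intended.

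**2. Effect on the visit outcome.** Compared with urging every such man to attend, text triage can only leave the number of in-person visits equal or lower. The measured visit reduction therefore depends on which rule is followed.

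**3. Possible effect on the AE outcome.** A man texts that he suspects an AE, which makes him a text responder. If he replied on Day 2, 7 or 14, he is in the denominator without an examination. If the nurse settles the matter by text, no provider grades it before Day 14. If it has resolved by Day 14, or he does not attend, it need not reach the numerator. Control men are scheduled for review on Days 2 and 7 and traced if absent, so this particular route does not exist for them.

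**4. Scale of one event**

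Inputs from the sample-size paragraph: margin 1.6 points, 2wT cutoff 2%, one-sided alpha 2.5%, power 90%, 10% loss, 361 per arm. The control rate of 0.4% is inferred as 2% − 1.6%, because Table 2 is not shown.

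- Plan's figure: n = (1.960 + 1.282)² × 2 × 0.004 × 0.996 / 0.016² ≈ 327.04, rounded up to 328 evaluable per arm; 328 × 1.10 = 361. The stated size is reproduced.
- Evaluable men after 10% loss: 361 × 0.9 ≈ 325.
- Expected AEs per arm: 325 × 0.004 = 1.3; at the 2% cutoff, 325 × 0.02 = 6.5.
- One uncounted AE: 1/325 = 0.31 points; 0.31/1.6 = 19% of the margin.

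**5. Sensitivity only.** The share of true 2wT AEs that is recorded is an assumption; the documents give none. With true rates of 2% (2wT) and 0.4% (control) and 325 men per arm, exact binomial enumeration gives the chance that the upper 95% limit falls below 1.6 points, which would wrongly declare non-inferiority:

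| 2wT AEs recorded (assumed) | Wald limit | Newcombe limit |
|---|---|---|
| 100% | 5.3% | 1.4% |
| 90% | 8.2% | 2.3% |
| 80% | 12.7% | 3.8% |
| 70% | 19.2% | 6.2% |
| 50% | 40.2% | 16.1% |

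These rows model under-recording from any cause. They do not estimate how much of it the text rule would produce, and the level depends on the interval chosen. The protocol names Fisher's exact test.

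**The case against.** The strongest reply is that the passages can be read as a sequence: the nurse texts first, and a man who is still concerned is then urged to attend. Section 4 also plans a situation analysis to set standards for text replies and in-person review, and Section 9 lists a texting flow chart, scripts and a clinical SOP that are not shown and may state the rule. This explains how the wording might have arisen. It does not make a conditional and an unconditional instruction agree, and appendices cannot repair the protocol's own text.

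The reply is much stronger against any claim of established bias.

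- A reader might infer that text triage lowers the AE count in the 2wT arm. The documents support only that it could. Both arms are asked to a Day 14 review meant to verify AE reporting, with an airtime credit for attending. 2wT men may attend at any time. The nurse asks about severity, and only moderate or severe AEs count. Daily prompting for 14 days may also bring out AEs that scheduled visits would miss, so the net direction is unknown. These safeguards limit the risk without removing it: attendance at Day 14 is requested rather than ensured, and some AEs may have resolved by then.
- A reader might infer that each site chooses its rule. Section 4 and the training section of Section 5 give text communication to one study nurse.
- A reader might take the background's expectation that more than 80% avoid visits to mean that about 20% of men fall under the rule. The remainder in that statement are men who attend in person, not men settled by text.
- Fewer visits are the intended effect of 2wT and not in themselves a bias.

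**Conclusion.** The inconsistency is in the protocol's text and is more than clerical, because the rule defines the intervention and the stated safeguard. Its effect on the visit outcome is direct, with a size the documents do not give. Its effect on the AE outcome is possible and not demonstrated: it needs an AE that is settled by text and then not seen at Day 14, and nothing in the documents says how often that would happen.

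The 0.31 points per event assumes 325 evaluable men. It shows that a very small number of uncounted AEs would matter when about 1.3 per arm are expected at the inferred 0.4% rate. It does not show that any would be missed. The error rates in the sensitivity table rest on assumed recording shares and should not be quoted as properties of this design. The sample size is unaffected.

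**What to change.** 1. Reconcile Sections 2, 3, 4 and both places in Section 5 to one rule for an affirmative text, chosen by the investigators. Carry it into the texting flow chart, scripts and clinical SOP.
2. Log every affirmative text with its date and disposition: examined in person or settled by text. The planned secondary outcome on time from AE text to follow-up already needs most of this linkage, and a calls/texts recording sheet is listed among the appendices.
3. At the Day 14 review, have the provider record in both arms, with the same question, whether any problem since surgery met the moderate or severe definition. Count it if it did and it is not already in the routine records. Asking only 2wT men who texted would create a new difference in ascertainment between the arms.

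The cost is protocol wording, one disposition field in the texting database and one item in the Day 14 register. Depending on the rule chosen, the visit reduction may look slightly smaller. Grading a resolved problem from history is less certain than examination, but the uncertainty would apply to both arms.
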